## Abstract

**Background:**

Generative artificial intelligence (GenAI) has the potential to revolutionise healthcare delivery. The nuances of real-life clinical practice and complex clinical environments demand a rigorous, evidence-based approach to ensure safe and effective deployment of AI.

**Methods:**

We present a protocol for the systematic evaluation of large language models (LLMs) as GenAI chatbots within the context of clinical microbiology and infectious diseases clinical consultations. We aim to critically assess recommendations produced by four leading GenAI models, including Claude 2, Gemini Pro, GPT-4.0, and a GPT-4.0-based custom AI chatbot.

**Discussion:**

A standardised, healthcare-specific, universal prompt template is developed to elicit clinically impactful AI responses. Generated responses will be graded by two panels of practicing clinicians, encompassing a wide spectrum of domain expertise in clinical microbiology and virology, as well as infectious diseases. Evaluations will be performed using a 5-point Likert scale across four clinical domains: factual consistency, comprehensiveness, coherence, and medical harmfulness. Our study will offer insights into the feasibility, limitations, and boundaries of GenAI in clinical consultations, providing guidance for future research and clinical implementation. Ethical guidelines and safety guardrails should be developed to uphold patient safety and clinical standards.

## Introduction

With an aging global population, ever increasing healthcare demands and the rapid evolution of healthcare technologies, effective integration of artificial intelligence (AI) into clinical workflow and decision-making processes have become a focal point of research and debate. GenAI has demonstrated significant potentials in understanding natural language and addressing cognitive tasks. [1] The prospects of GenAI replacing or augmenting physician tasks, particularly in telemedicine where information exchange is primarily text-based, has prompted investigations into their practicality and safety in clinical consultations. [2]

Preliminary investigations have demonstrated the potentials for AI in managing various infectious disease syndromes (e.g., bloodstream infections and brain abscesses), however, concerns remain about the reliability, safety, and ethics of GenAI adoption in clinical practices.[3–5] This study is among the first to systemically evaluate state-of-the-art GenAI large language model (LLM) chatbots, including a custom AI chatbot (custom bot) integrated with domain-specific medical literature. In addition, this study employs a novel self-developed healthcare-specific prompt template purposely designed to examine AI chatbot performances in complex real-life clinical scenarios. A unique dual-tier evaluation system that includes both practicing specialists and non-specialist resident trainees is also implemented in the evaluation process to offer a comprehensive assessment from multiple levels of domain expertise and clinical experience.

The objective of this protocol is to critically assess the clinical accuracy, coherence, comprehensiveness, and safety of recommendations provided by AI chatbots. This research aims to contribute to the ongoing discourse on the role of GenAI in healthcare and to aid in the development of guidelines to ensure the safe and effective deployment of GenAI in clinical microbiology and infectious diseases.

## Materials and methods

This project aims to evaluate the potential role of AI chatbots to assist clinicians by providing immediate analysis and suggestions to enhance and augment clinical practice and workflow. The protocol employs a universal standardised prompt template to compare between AI chatbot responses against real-life clinical scenarios. Generated responses will be evaluated by a panel of practicing clinicians [specialists (n =  3); resident trainees (n =  3)] using a 5-point Likert scale. [6] Human evaluators will serve as domain experts with specific knowledge in clinical microbiology and virology, as well as internal medicine and clinical infectious diseases (Fig 1).

**Fig 1 pone.0300487.g001:**
[figure not shown]
Materials and methods. AI: artificial intelligence.

### Data source

During the pre-defined study period, real-life clinical notes will be extracted retrospectively from the digital depository (in-house software) of the Department of Microbiology, Queen Mary Hospital (QMH), Hospital Authority, Hong Kong. Within the study period, 40 clinical notes derived from four clinical microbiologists [10 clinical notes per microbiologists; fellows (n =  2) and resident trainees (n =  2)] will be included consecutively.

For the inclusion criterion, only new in-patient consultation referrals received by the Department of Microbiology (QMH) during the study period will be included. As for exclusion criteria, duplicated consultations will be removed to limit redundancy and potential data skew. Follow-up assessments and reviews during the same clinical episode will be excluded to focus on initial management approach, diagnostic assessments, and treatment decisions. The inclusion and exclusion criteria are carefully designed to maintain clarity and data integrity and to ensure a well-defined analytical framework.

### Data preprocessing

Data preprocessing will be conducted manually by [name] and [name] To maintain authenticity of the original clinical notes, preprocessing procedures are designed to be minimal, where the clinical context, syntax and written styles of the initial documents are retained as far as possible. Patient identifiable information is removed. Names of medical institutions are excluded or anonymised. Medical terminologies are standardised, where abbreviations and non-universal short forms are converted into their full terms (e.g., expanded abbreviations: from ‘c/st’ to ‘culture’, ‘T/F’ to ‘pending results’, ‘CMV D+R-’ to ‘cytomegalovirus seropositive donor and seronegative recipient’). Appropriate International System (SI) of units are included for quantitative results to allow clear interpretations (e.g., adding ‘g/dL’ to the values of haemoglobin). For chronological structuring, relevant dates are included in the clinical scenarios. Moreover, contents related to the clinical impression and management approach of the scenario will be removed to minimise input biases. Lastly, to ensure structural uniformity across all clinical scenarios, the contents will be outlined systematically into five categories: “Basic demographics & Underlying medical conditions”, “Current admission”, “Physical examination findings”, “Investigation results” and “Antimicrobials & Treatments”.

### Prompt template

A standardised, domain-specific, unconditional, zero-shot prompt template was developed for this study (Fig 2). All clinical scenarios will be processed as separate files along with the standardised prompt template. [7]

**Fig 2 pone.0300487.g002:**
[figure not shown]
Healthcare-specific standardised prompt template.

The prompt template begins with a system message (base prompt) that defines the behaviour of the model and prescribes the style of response within pre-defined boundaries. In this study, AI chatbots are primed as “an artificial intelligence assistant with expert knowledge in clinical medicine, infectious disease, clinical microbiology and virology”.

In the design of the prompt template, a Performed-Chain of Thought (P-COT) prompting approach will be adopted. [8] The analytical process will be broken down into clinically meaningful segments and sub-tasks, to allow a logical sequence of prompts, where the outputs permeate sequentially throughout the step-by-step process. [9, 10]

Initially, the chatbot is instructed to identify and classify active clinical problems, and list any immediate life-threatening complications, ensuring that each complication logically stems from the reviewed issues. Following this, the chatbot suggests anticipated physical examination findings which correlate to the identified clinical problems. Subsequently, it formulates a list of probable differential diagnoses by synthesising information from the available data which aligns with the gathered clinical evidence. Furthermore, the chatbot is directed to provide a detailed series of investigations for the listed differentials, including justifications for each recommended test, ensuring that every diagnostic step is supported by robust clinical rationale. Moving forward, a comprehensive management plan is constructed by the chatbot, incorporating strategies for the prevention and management of complications specific to the clinical situation and medical context identified throughout its analysis. Finally, the chatbot encapsulates its analysis and recommendations in a concise summary.

This structured, step-by-step approach not only enhances the chatbot’s ability to generate clinically relevant and accurate responses but also promotes transparency in its decision-making process, ensuring traceability, comprehensiveness and clarity in the final AI-generated recommendations.

At the end of the prompt, the chatbots will be further instructed to follow the prompt instructions strictly to reinforce the specific model persona for the desired output. [11] Output formats are standardised throughout the prompt chain; where certain AI model(s) does not support table generation, the outputs will be reformatted into lists manually.

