### Blinding, randomisation and data compilation

The dataset will include 40 unique clinical scenarios, individually processed four AI chatbots (i.e., Claude 2, Gemini Pro, GPT-4.0 and cGPT-4), resulting in 160 total outputs. All study authors (except [name]) and human evaluators will be blinded to the original authors of the clinical scenarios, as well as the identity of GenAI model for the chatbot output.

To ensure objective assessments and minimise evaluator biases, all investigators, except [name], will be blinded to the clinical scenarios and chatbot outputs. Dual-level randomisation will be employed, where the clinical scenarios will be randomised before being inputted into the chatbots, and the corresponding AI-generated responses will be further randomised before being subjected to human evaluation. Randomised clinical scenarios and corresponding AI chatbot outputs will be uploaded onto the Qualtrics survey platform (Qualtrics, Utah, U.S.) for human evaluation and grading. Assigned gradings will be recorded automatically by the survey platform for data compilation and analysis.

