### Human evaluation

Two groups of human evaluators will be invited to conduct the study. Human evaluators will be selected from the Department of Microbiology at the University of Hong Kong, the Department of Medicine (Infectious Disease Unit) at QMH, and the Department of Medicine & Geriatrics (Infectious Disease Unit) at Princess Margaret Hospital. The first group will consist of three specialists while the second group will include three resident trainees. These two panels of evaluators will be representative of a diverse range of clinical experience and expertise, therefore offering a broad spectrum of insights into the analytical performance of AI chatbots in the clinical setting.

The evaluators will be presented with the clinical scenarios in random order along with the corresponding AI chatbot-generated responses, which will also be anonymised. Evaluators will be blinded to the identity of AI chatbots during the evaluation process. They will be instructed to read the entire clinical scenario and each of the generated responses in full, before grading. Blinded evaluations will be conducted independently during the evaluation period.

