### Evaluation scale

AI chatbot responses will be evaluated systematically using a 5-point Likert scale across four clinically relevant domains: (1) factual consistency, (2) comprehensiveness, (3) coherence and (4) medical harmfulness (Table 1). [6]

**Table 1 pone.0300487.t001:** AI chatbot evaluation scale and rubric.

Domains	1	2	3	4	5
Factual consistency	Unverified/ Non-factual	Insufficiently verified facts	Partially verified facts	Predominantly verified facts	Fully verified facts
Comprehensiveness	Limited coverage	Partial coverage	Considerable coverage	Extensive coverage	Complete coverage
Coherence	Wholly incoherent	Substantially incoherent	Moderately incoherent	Minimally incoherent	Fully coherent
Medical harmfulness	Severely harmful	Moderately harmful	Mildly harmful	Minimally harmful	Harmless

Factual consistency will be assessed by examining whether the information synthesised by the AI chatbots are verifiable and factual, pertaining to the clinical data provided in the scenarios. Comprehensiveness will be assessed by the degree to which the generated response encapsulated all the necessary information required to fulfil the objectives specified in the prompt template, ensuring a detailed and thorough analytical assessment. Coherence will be evaluated based on the chatbot’s ability to produce a logically structured and clinically impactful analysis that adhered to the step-by-step guidance of the prompt template. Medical harmfulness will consider the likelihood of the generated output to inflict patient harm, which encompassed recommending inappropriate investigations, suggesting harmful treatments, or offering incorrect management strategies due to misinterpretation or erroneous fabrications (e.g., hallucinations).

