### Outcomes

The primary outcome will be the composite score comparisons between AI chatbots. Secondary outcomes will include domain-level comparisons across generated responses, and correlation analysis between composite scores and characteristics of clinical scenarios and AI chatbot output.

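### Hand conversion to lists is tied to chatbots that cannot make tables, so layout may mark groups of chatbots to the raters and editing may enter the coherence score; the article should fix one layout for all 160 outputs

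*Protocol article*

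**What the plan says.** The relevant sentence closes the Prompt template section of the protocol article, after Fig 2. Its first half gives the aim: "Output formats are standardised throughout the prompt chain". Its second half gives the procedure: "where certain AI model(s) does not support table generation, the outputs will be reformatted into lists manually". It does not say whose outputs are meant, how many models are concerned, who edits, by what rule, or whether the content is checked as unchanged.

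The Human evaluation section states the masking: "Evaluators will be blinded to the identity of AI chatbots during the evaluation process". It also describes what raters see: "The evaluators will be presented with the clinical scenarios in random order along with the corresponding AI chatbot-generated responses, which will also be anonymised". The section on blinding, randomisation and data compilation adds random ordering of scenarios and responses and upload to a survey platform. Neither section describes a step that gives all responses a common layout.

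The Evaluation scale section scores coherence on the ability to "produce a logically structured and clinically impactful analysis that adhered to the step-by-step guidance of the prompt template". The Composite score evaluation section sums the four domain means, and the Outcomes section makes that composite primary: "The primary outcome will be the composite score comparisons between AI chatbots".

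**The concern.** Removing names and shuffling order mask a label. They do not mask something visible in the response itself. If some chatbots always appear as lists and others always as tables, a rater who reads the responses to scenario after scenario can learn to recognise the same source or group of sources. The rater need not know the product name. An impression formed on earlier scenarios can carry over to later ones.

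The second route is the editing. Text restructured by a member of the study team is no longer purely the chatbot's work, and the amount of restructuring would depend on which chatbot wrote it. Logical structure is part of what coherence scores, so the edit could help or hurt the property being measured.

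The discussion presents blinding and randomisation as the plan's answer to evaluator bias. The limitations listed there mention neither layout nor hand editing.

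**Working it through.** **Inputs.** "The dataset will include 40 unique clinical scenarios, individually processed four AI chatbots" (section on blinding, randomisation and data compilation). Four domains, each scored 1 to 5 (Table 1). Composite = sum of the four domain means, range 4 to 20 (Composite score evaluation). The number of models without table support, k, is not given, so it is varied below.

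**Step 1: reproduce the stated total.** 40 scenarios × 4 chatbots = 160 outputs, as the article says. Each chatbot supplies 40/160 = 25%.

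**Step 2: how much is edited if only the affected models are converted.** Edited outputs = 40k. Chatbot pairs that compare a list with a table = k(4 − k), out of 4 × 3 / 2 = 6 pairs in the post-hoc comparisons.

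| k | Edited outputs | Share of 160 | List-versus-table pairs |
|---|---|---|---|
| 1 | 40 | 25% | 1 × 3 = 3 of 6 |
| 2 | 80 | 50% | 2 × 2 = 4 of 6 |
| 3 | 120 | 75% | 3 × 1 = 3 of 6 |

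If instead all outputs are converted, 160 of 160 are edited, no pair differs in layout, and the cue disappears.

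**Step 3: can analysis separate the two effects?** On the selective reading, the list indicator equals the sum of the indicators of the affected chatbots. It is an exact linear function of the chatbot factor and adds no rank to the model. No covariate adjustment can split a layout effect from a chatbot effect in the list-versus-table pairs. Pairs within the same layout are not confounded by table versus list.

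**Step 4: path to the primary outcome.** The composite is a plain sum, so a shift of d in mean coherence, with the other domains unchanged, moves the mean composite by d. Coherence spans 5 − 1 = 4 of the 20 − 4 = 16 points of composite range, or 25%. The documents give nothing from which d could be estimated; it may be zero.

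**Step 5: a secondary analysis.** The Correlation analysis section relates composite scores to output word counts. Turning a table into a list can change the count, for instance when column headings are repeated in each item. The article does not say whether the edited or unedited text is counted.

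**The case against.** The strongest reply is that the sentence opens with standardised formats and leaves the outputs unqualified. It can therefore mean that every chatbot's responses become lists as soon as one model cannot make tables. On that reading the main remedy is already the plan. This stands as a possible reading, so the layout cue has to be stated conditionally. It does not settle the matter. The condition is attached to particular models, which makes their outputs the natural object, and no later section describes a common layout. Even on the all-lists reading, 160 outputs are edited by hand with no stated rule.

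A reader might go further and infer that layout identifies the chatbot and that blinding has failed. The documents do not support this. With two or three affected models, a list marks a group and not one chatbot. With one, it reveals the product only to a rater who knows which product lacks tables, and nothing says raters know that.

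Three further points have some force:

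- A model that cannot make tables looks different before any editing, and clean lists may make it less conspicuous. That is an argument for standardising all four.
- Any fixed trait of a chatbot, such as style or length, is inseparable from the chatbot, and native tables could count as performance. Style and length are the chatbot's own, however, whereas the list conversion is made by the study team.
- The coherence definition concerns logical structure and following the prompt steps, and does not name visual layout. How much of a response is tabular depends on the prompt in Fig 2, which is not shown. The effect may therefore be small.

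A detailed editing rule could also sit in the full protocol. Whether all four chatbots share one layout is different: the article addresses it in a way that can be read against its own aim of standardisation.

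**Conclusion.** The point holds as a risk that should be removed or reported. On the more natural reading, table versus list is fixed by chatbot, visible to raters over 40 scenarios and untouched by anonymising or randomising. Between 40 and 120 of the 160 outputs would be hand-edited, and 3 or 4 of the 6 pairwise comparisons would mix layout with chatbot. Any resulting shift in coherence passes one for one into the primary composite.

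This rests on two assumptions: that conversion is selective, and that one to three models are affected. The article confirms neither. It does not follow that raters were unmasked or that the composite is biased by a particular amount.

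**What to change.** State in the Prompt template section, and repeat in the section on blinding, that all 160 outputs from all four chatbots are put into one common list layout before upload. The conversion should follow one fixed rule that preserves content and should be applied by someone who does not rate. Keep the unedited text and use it for the word counts.

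The status section says evaluators are already reviewing, so this may come too late for some or all outputs. For those graded in mixed layouts, report which chatbots were reformatted, and qualify the coherence and composite comparisons between list and table chatbots as possibly affected by layout. If all outputs were in fact converted, one sentence saying so, with the rule used, closes the question of the layout cue.

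The cost is a few hours of reformatting. The downside is that native table presentation is no longer part of what is evaluated.

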### AI chatbots

AI chatbots will be accessed via Poe (Quora, California, U.S.), a third-party subscription-based AI software platform. We will evaluate the responses generated from Claude 2 (Anthropic, California, U.S.), Gemini Pro (Google DeepMind, London, U.K.), GPT-4.0 (OpenAI, California, U.S.), and a custom bot based on GPT-4.0 (cGPT-4).

The custom bot will be created through the “Create bot” function within the Poe interface. GPT-4 is selected as the foundation model for the custom bot. Four widely recognised clinical references will be integrated into the knowledge base of the custom bot, which will include: Török, E., Moran, E. and Cooke, F. (2017) *Oxford Handbook of Infectious Diseases and Microbiology*. Oxford University Press. [12]; Mitchell, R.N., Kumar, V., Abbas A.K. and Aster, J.C. (2016). *Pocket Companion to Robbins & Cotran Pathologic Basis of Disease* (Robbins Pathology). Elsevier. [13]; Sabatine, M.S. (2022) *Pocket Medicine: The Massachusetts General Hospital Handbook of Internal Medicine*. Lippincott Williams & Wilkins. [14] and Gilbert, D.N., Chambers, H.F., Saag, M.S., Pavia, A.T. and Boucher, H.W. (editors) (2022) *The Sanford Guide to Antimicrobial Therapy 2022*. Antimicrobial Therapy, Incorporated. [15] These references aim to provide domain-specific knowledge to inform the generated responses by the custom bot.

The AI chatbot response variability is configured to the pre-determined temperature setting as defined by Poe, which will be most applicable to the general user. Temperature, a hyperparameter in the GenAI model, determines the degree of randomness in its responses. A lower setting produces more predictable responses while a higher setting produces answers with greater variability and creativity. [16] The preset temperature configurations for the AI chatbots are as follow: Claude 2 at 0.5, GPT-4 at 0.35, and the custom bot at 0.35; however, the exact temperature setting for Gemini Pro is not publicly available.

Each clinical scenario will be presented as a new chat using an unconditional prompt to ensure unbiased outputs. All scenarios will be inputted by [name] and processed on a pre-specified date to ensure output consistency.

